### Study parameters

We will collect the following parameters: 1) information about the index ICH, including date, National Institutes of Health Stroke Scale score [46], location and volume of the ICH assessed on computed tomography (CT) or magnetic resonance imaging (MRI), antithrombotic medication and INR; 2) previous medical history, including cardiovascular risk factors and previous cardiovascular events, and all variables comprising the CHA_2_DS_2−_VASc [8] and HAS-BLED [47] scores; 3) blood levels of haemoglobin, liver enzymes, and creatinine, and calculated glomerular filtration rate; 4) at the time of randomisation: the score on the mRS, blood pressure, and the Informant Questionnaire on Cognitive Decline in the Elderly (IQCODE), to screen for cognitive decline prior to the index ICH [48].

### Study procedures

After written informed consent will have been obtained, the patient will be randomised. We will collect imaging data obtained in routine clinical care for central reading. At inclusion, the IQCODE will be administered to a person who is close to the patient (partner, family member or friend).

After randomisation, the patient will receive written information related to the assigned treatment to maximise treatment adherence, consisting of a patient alert card for this trial in general and a specific patient alert card for apixaban users. The investigator will send a letter to the general practitioner that will mention inclusion in this trial.

At 1 (±7 days), 6 (±14 days), and 12 (±28 days) months and subsequently every 12 months (±28 days), follow-up visits will be scheduled (Fig. 2).

**Fig. 2 Fig2:**
[figure not shown]
Flowchart of study procedures

The treating physician or his representative will perform each follow-up visit. Patients will be asked to fill out the Modified Morisky Scale [49] for treatment adherence. Blood pressure will be measured. Disability will be measured with the mRS. Patients will be questioned about the occurrence of outcome events or (other) serious adverse events (SAEs) in the preceding period.

### Study outcomes

The primary outcome is the combination of vascular death or non-fatal stroke (cerebral infarction, ICH, or subarachnoid haemorrhage) during follow-up. Secondary outcomes will be: vascular death, death from any cause, all stroke, ischaemic stroke, ICH, other major extracranial haemorrhage, any intracranial haemorrhage other than ICHd, systemic embolism, myocardial infarction, and functional outcome as assessed with the score on the mRS at 6 and 12 months; annually thereafter; and at the end of the study. Definitions of the clinical events comprising the study outcomes are shown in Table 3.

**Table 3 Tab3:** Event definitions

Ischaemic stroke	Clinical evidence of the sudden onset of a new neurological deficit, or an increase in an existing deficit, persisting for more than 24 hours, without evidence of a intracerebral haemorrhage on a CT or MRI scan or at post-mortem investigation
Intracerebral haemorrhage	Clinical evidence of the sudden onset of a new neurological deficit, or an increase in an existing deficit, persisting for more than 24 hours, with a corresponding intracerebral haemorrhage on a CT or MRI scan or at post-mortem investigation
Unclassified stroke	Clinical evidence of the sudden onset of a new neurological deficit, or an increase in an existing deficit, persisting for more than 24 hours, without imaging or post-mortem investigations performed
Subarachnoid haemorrhage	Subarachnoid haemorrhage (SAH) demonstrated by CT, lumbar puncture, or at post-mortem investigation
Myocardial infarction	Evidence of myocardial necrosis in a clinical setting consistent with acute myocardial ischemia. Under these conditions any one of the following criteria meets the diagnosis for MI [51]:
	● Detection of a rise and/or fall of cardiac biomarker values (preferably cardiac troponin) with at least one value above the 99th percentile upper reference limit and with at least one of the following:
	○ Symptoms of ischemia
	○ New or presumed new significant ST-segment-T wave changes or new left bundle branch block (LBBB)
	○ Development of pathological Q waves in the ECG
	○ Imaging evidence of new loss of viable myocardium or new regional wall motion abnormality
	○ Identification of an intracoronary thrombus by angiography or autopsy
	● Cardiac death with symptoms suggestive of myocardial ischemia and presumed new ischemic ECG changes or new LBBB, but death occurred before cardiac biomarkers
Vascular death	Death from cerebral infarction; intracerebral, subarachnoid, epidural, or subdural haemorrhage; unclassified stroke; myocardial infarction; extracranial haemorrhage; or systemic embolism, fatal arterial or gastric bleeding, terminal heart failure, fatal pulmonary embolism, and sudden death, defined as death within 1 hour after onset of symptoms
Major extracranial haemorrhage	Major extracranial bleeding will be defined using the ISTH criteria [52];
	1) Fatal bleeding, and/or
	2) Symptomatic bleeding in a critical area or organ, such as intraspinal, intraocular, retroperitoneal, intra-articular or pericardial, or intramuscular with compartment syndrome, and/or
	3) Bleeding causing a fall in haemoglobin level of 1.24 mmol L^−1^ or more, or leading to transfusion of 2 or more units of whole blood or red cells
Clinically relevant non-major bleeding	Clinically relevant non-major bleeding will be defined as acute clinically overt bleeding that does not satisfy additional criteria required for the bleeding event to be defined as a major bleeding event and meets at least one of the following criteria [53]:
	● Hospital admission for bleeding
	● Physician-guided medical or surgical treatment for bleeding
	● Change in antithrombotic (anticoagulant or antiplatelet) therapy
Intracranial haemorrhage	Intracerebral haemorrhage (see above), SAH (see above), subdural haemorrhage: evidence of a subdural haematoma on a CT or MRI scan or at post-mortem investigations; epidural haematoma: evidence of an epidural haematoma on a CT or MRI scan or at post-mortem investigations
Systemic embolism	The diagnosis of systemic embolism requires a clinical history consistent with an acute loss of blood flow to a peripheral artery (or arteries) supported by evidence of embolism from surgical specimens, post-mortem investigations, angiography, vascular imaging, or other objective testing

*CT* computed tomography, *ECG* electrocardiogram, *MRI* magnetic resonance imaging

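### The itemised primary outcome leaves out non-fatal unclassified stroke, although fatal unclassified stroke counts and other sections set no such limit

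*Protocol article*

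**What the plan says.** The Study outcomes section gives the only itemised definition of the primary outcome: "The primary outcome is the combination of vascular death or non-fatal stroke (cerebral infarction, ICH, or subarachnoid haemorrhage) during follow-up". The bracket names three types and has no word marking them as examples.

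The section then says "Definitions of the clinical events comprising the study outcomes are shown in Table 3". Table 3 has four stroke entries: ischaemic stroke, intracerebral haemorrhage, unclassified stroke and subarachnoid haemorrhage. Unclassified stroke is a sudden new or worsened deficit "persisting for more than 24 hours, without imaging or post-mortem investigations performed". The vascular death entry includes "Death from cerebral infarction; intracerebral, subarachnoid, epidural, or subdural haemorrhage; unclassified stroke; myocardial infarction; extracranial haemorrhage; or systemic embolism", so a fatal unclassified stroke is a primary outcome event.

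Elsewhere the primary outcome appears without a list. The abstract (Background and Methods/Design), the closing paragraph of the Background, Statistical analysis and Interim analyses all refer to vascular death or non-fatal stroke and stop there. The secondary outcome of all stroke is not itemised either.

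**The concern.** The article defines four kinds of stroke and lists three of them as non-fatal primary events. An adjudicator who applies the bracket as written would code a survived, uninvestigated deficit as unclassified stroke and then not count it. One who works from the statistical section would count it. No rule says which prevails.

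The main aim is to estimate the rate of this outcome in each arm to inform a phase III trial, and the same outcome drives the interim looks at 50, 100 and 150 patient-years. With about 10 events per arm as the planning case, each event moves the rate by about one tenth.

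Such events are plausible. Study procedures describes only the collection of routine-care imaging, and the article states no scan at suspected stroke. After month 12 the visits are yearly and patients are asked about the preceding period, so some strokes may come to light late and without a scan.

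**Working it through.** **Step 1. The definitions side by side (Study outcomes, Table 3).**

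| Event | Non-fatal: in the bracketed list? | Fatal: counted as vascular death? |
|---|---|---|
| Ischaemic stroke (cerebral infarction) | Yes | Yes |
| Intracerebral haemorrhage | Yes | Yes |
| Subarachnoid haemorrhage | Yes | Yes |
| Unclassified stroke | No | Yes |

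Only the last row differs between columns. Under the unlisted wording in the other sections, its first cell would be Yes.

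**Step 2. Could another entry in Table 3 take in the event?** Ischaemic stroke is worded as a deficit "without evidence of a intracerebral haemorrhage on a CT or MRI scan or at post-mortem investigation", which does not expressly require a scan. If an uninvestigated stroke went there, the two entries would overlap and the unclassified one would have no purpose. It would also put possible haemorrhages into the ischaemic stroke outcome, which Interim analyses treats as the main efficacy component, with ICH as a harm. Subarachnoid haemorrhage is "Subarachnoid haemorrhage (SAH) demonstrated by CT, lumbar puncture, or at post-mortem investigation", so a case proven by lumbar puncture alone counts without a scan. The gap therefore concerns unclassified strokes, not every stroke without imaging.

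**Step 3. The plan's own figure.** Sample size estimation gives 10 events in 100 patient-years with a 95% CI of 4.9 to 17.6. The exact binomial (Clopper-Pearson) interval for 10 of 100 is 4.90 to 17.62, so the figure reproduces. The exact Poisson interval is 4.80 to 18.39; the difference does not bear on this point.

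**Step 4. Size of the loss.** Inputs:
- E = 10 planning events per arm (Sample size estimation).
- p = share of those events that are non-fatal strokes: not given; assumed 0.5 to 1.0.
- f = share of non-fatal strokes that are unclassified: not given; assumed 0.02 to 0.10.

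Events lost per arm = E × p × f. The factor p is needed because some of the 10 events are vascular deaths, and these are not lost.

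| p | f = 0.02 | f = 0.05 | f = 0.10 |
|---|---|---|---|
| 0.5 | 0.10 | 0.25 | 0.50 |
| 0.7 | 0.14 | 0.35 | 0.70 |
| 1.0 | 0.20 | 0.50 | 1.00 |

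The loss is 0.1 to 1 event per arm, or 1% to 10% of the rate. The top value needs every primary event to be a non-fatal stroke.

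**Step 5. Against the precision of the trial.** By the same exact binomial method, 9 events give 4.2 to 16.4, 10 give 4.9 to 17.6 and 11 give 5.6 to 18.8. A change of one event is small beside any of these intervals.

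For the hazard ratio, 10 events per arm give an approximate standard error of the log of √(1/10 + 1/10) = 0.45. The 95% limits then lie a factor of exp(1.96 × 0.447) = 2.4 either side. If the largest loss fell wholly in one arm, the ratio of event counts would move by a factor of 9/10 = 0.90, or 10/9 = 1.11 if it fell in the other.

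**The case against.** The bracket need not be a closed list. Every other statement of the primary outcome is unrestricted, an unclassified stroke is still a stroke, and Table 3 is introduced as defining the events that make up the outcomes. No passage tells the adjudicators to exclude such an event. This stands in part: the closed reading is the natural one for a bracket without a word such as including, but it is not the only one. That makes the point an inconsistency to reconcile rather than a proven exclusion.

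Requiring confirmation for non-fatal events is defensible in survivors of ICH, where worsening of an existing deficit can qualify and a death must in any case be assigned a cause. That could justify the asymmetry, but the article does not give it as a reason, and it would not explain the unrestricted wording elsewhere.

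The secondary outcome of all stroke, on its plain meaning, already covers the category. This stands; it needs confirming, not correcting.

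A patient whose unclassified stroke is not counted may later have a listed event, so in a time-to-event analysis some events are delayed rather than lost. This also stands and makes the loss in the working an upper figure for given p and f.

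A reader might infer that the omission biases the hazard ratio, because clinicians who know the allocation may scan patients on an anticoagulant more readily. The documents do not support that: they give no scanning frequency, overall or by arm. Safety reporting requires suspected thromboembolic and haemorrhagic events to be reported in both arms, so reporting does not depend on a scan. The open-label design makes a difference between arms possible and no more.

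**Conclusion.** The point holds as an internal inconsistency in the primary outcome. Taken literally, the itemised definition drops a non-fatal unclassified stroke and keeps a fatal one, and it conflicts with the unrestricted wording in the abstract, objectives, Statistical analysis and Interim analyses. Because the article itself states both the outcome and the event definitions, this is not detail left to the analysis plan.

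The size is about 0.1 to 1 event per arm. It rests wholly on the two assumed ranges, since the article gives neither the frequency of unclassified stroke nor the split of primary events between deaths and strokes.

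Two stronger readings should not be drawn. One is that all strokes without imaging count only when fatal; subarachnoid haemorrhage shown by lumbar puncture is an exception. The other is that the trial's estimates are materially compromised; the possible shift is far inside the precision of a phase II estimation study. Severity is minor to moderate: the effect is small, but it touches the primary outcome and is easily removed.

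**What to change.** Word the primary outcome as non-fatal stroke (cerebral infarction, ICH, subarachnoid haemorrhage, or unclassified stroke). State that the secondary outcome of all stroke includes unclassified stroke, and point Statistical analysis and Interim analyses to this one definition. Settle it before events are adjudicated, so that the choice cannot depend on which events have occurred.

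The cost is a few words in the outcome definition and the adjudication form, since the category already exists. The downside is that a few events without imaging confirmation enter the count; a sensitivity analysis of the primary outcome excluding non-fatal unclassified strokes would show whether they matter. If the exclusion is intended, the article should say so, give the reason and bring the other sections into line.

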### Eligible patients

Patients with AF who recently had an ICH during the use of anticoagulation, in whom there is clinical equipoise regarding the optimal medical treatment for the prevention of stroke, are eligible for participation in this trial. The ICH should have occurred between 7 and 90 days prior to randomisation. The CHA_2_DS_2_-VASc score should be 3 or higher [8] and the score on the modified Rankin Scale (mRS) [45], as a measure for disability, 4 or lower. Detailed eligibility criteria are shown in Table 1.

**Table 1 Tab1:** Eligibility criteria

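### Table 3's stroke definitions do not separate new bleeding from the index haematoma, so some events could fit no stroke category or be given the wrong stroke type

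*Protocol article*

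**What the plan says.** Under Eligible patients, "The ICH should have occurred between 7 and 90 days prior to randomisation". Table 1 requires that haemorrhage to be documented on CT or MRI.

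Under Study outcomes, the primary outcome is the "combination of vascular death or non-fatal stroke (cerebral infarction, ICH, or subarachnoid haemorrhage) during follow-up". The same section makes Table 3 operative: "Definitions of the clinical events comprising the study outcomes are shown in Table 3".

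In Table 3, ischaemic stroke, ICH and unclassified stroke share one clinical condition: "Clinical evidence of the sudden onset of a new neurological deficit, or an increase in an existing deficit, persisting for more than 24 hours". They differ only in the imaging condition:

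- Ischaemic stroke: "without evidence of a intracerebral haemorrhage on a CT or MRI scan or at post-mortem investigation"
- ICH: "with a corresponding intracerebral haemorrhage on a CT or MRI scan or at post-mortem investigation"
- Unclassified stroke: "without imaging or post-mortem investigations performed"

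Under Study procedures, "We will collect imaging data obtained in routine clinical care for central reading". Study parameters lists the location and volume of the index ICH among the baseline data. Outcome adjudication describes a committee of two vascular neurologists and a cardiologist, blinded to allocation. None of these sections gives a rule for telling old blood from new.

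**The concern.** The imaging conditions would work in patients who start follow-up without blood on the scan. Here each participant starts follow-up with a haemorrhage at most 90 days old. The ischaemic stroke definition is failed by any evidence of ICH, and the ICH definition asks only that a haemorrhage match the deficit. So the index lesion can block the first label or satisfy the second.

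This matters because Sample size estimation gives the trial's main purpose as estimating the event rates for a phase III design. Interim analyses names ischaemic stroke as the main efficacy component and ICH as a main harm component of the composite. Ischaemic stroke and ICH are also separate secondary outcomes. A definition that can drop an infarct, or record one as a haemorrhage, weakens the estimates that the phase III design would draw on.

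**Working it through.** **Step 1: apply the printed wording to four cases.** Each patient has a sudden new or increased deficit lasting more than 24 hours and is scanned. The index haematoma is still visible, except in case D.

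| Case | Ischaemic stroke | ICH | Unclassified stroke | Result |
|---|---|---|---|---|
| A. New infarct, deficit unrelated to the index site | Fails: blood is evident | Fails: blood does not correspond | Fails: imaging was done | No category |
| B. New infarct that worsens the original deficit | Fails: blood is evident | Met: blood corresponds | Fails | ICH; stays in the composite under the wrong type |
| C. Original deficit worsens, no new bleed and no infarct | Fails: blood is evident | Met: blood corresponds | Fails | ICH without new bleeding |
| D. New infarct, index blood no longer visible | Met | Fails | Fails | Correct |

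The remaining stroke type, subarachnoid haemorrhage, does not take in case A.

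**Step 2: look for a clause elsewhere that closes the gap.** The Background names recurrent ICH as a secondary objective, but Table 3 contains no recurrence criterion. In the same table, several myocardial infarction criteria do ask for new or presumed new changes, so the qualifier was used where it was thought necessary. Central reading and adjudication are described without a comparison rule.

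**Step 3: the plan's own figure, for scale.** Sample size estimation gives 10 events in 100 patient-years with a 95% CI of 4.9 to 17.6. An exact Clopper-Pearson interval for 10/100 gives 4.90 to 17.62, which reproduces it. Each event wrongly lost or gained moves the rate by 1 per 100 patient-years, against an interval 17.6 − 4.9 = 12.7 wide.

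**Step 4: can the loss in case A be sized?** If a share *s* of the 10 events are ischaemic strokes and a fraction *f* of those fit no category, the counted events are 10 × (1 − *s* × *f*). The documents give neither *s* nor *f*.

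A rough bound for CT is possible under these assumptions, none of which comes from the documents:

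- index blood is visible for 6 weeks after the ICH;
- the hazard is constant;
- 3 to 7 of the 10 events are ischaemic strokes;
- every patient is randomised on day 7, the earliest day allowed.

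Mean follow-up is 100/50 = 2 years, or 104 weeks. The exposed time is 6 − 1 = 5 weeks, a fraction of 5/104 = 0.048. The expected loss is then at most 3 × 0.048 = 0.14 to 7 × 0.048 = 0.34 events per arm (0.24 with 5 strokes). It is zero for anyone randomised after day 42. A longer visible period would raise these figures.

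For MRI there is no comparable bound. The documents do not say how long index blood stays visible, or how often MRI would be the event scan.

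**The case against.** The strongest defence is context. The Background speaks of recurrent ICH, which in ordinary use excludes the index bleed. The adjudication committee reviews new outcomes. Every stroke definition except subarachnoid haemorrhage requires sudden onset and more than 24 hours' duration. The primary outcome uses the term cerebral infarction, which a proven infarct plainly is. Two vascular neurologists are unlikely to declare such an infarct a non-event, and a fuller protocol or adjudication document may hold a reading rule.

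Much of this stands. The loss needs both visible residual blood and a literal reading. The word requiring correspondence already stops the index lesion from counting as ICH when the deficit lies elsewhere. Some misread infarcts stay in the composite as ICH (case B), and fatal ones may still count through vascular death, whose definition includes death from cerebral infarction.

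It does not remove the point. Table 3 is stated to define the outcomes, and its wording is explicit rather than silent. An adjudicator who classifies cases A to C sensibly departs from it case by case, without a stated rule. A further document could help only by adding to or overriding the table.

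A reader might also infer that the gap favours one arm, because the protocol's ethical section expects fewer ischaemic strokes on apixaban. The documents do not support this. Lost infarcts remove events while case C adds them, neither frequency is given, and no net direction between arms can be derived.

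**Conclusion.** The definitions are fixed badly for this population. As printed, they allow a scanned infarct to fall outside every stroke category, and they allow worsening of the original deficit to be recorded as ICH without new bleeding. This follows from the wording and the eligibility criteria alone.

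The exposure is greatest for the division between ischaemic stroke and recurrent ICH, since cases A, B and C all distort it. The primary event rate is touched only by cases A and C, which pull in opposite directions. That effect is smaller and unquantified. It might be tempting to attach a number of lost primary events, or to call the primary rate seriously biased. The documents give no frequency for either, and the CT bound above is below half an event per arm under its assumptions.

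The conclusion assumes that index blood is still visible on some event scans and that adjudicators apply Table 3 as written.

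**What to change.** Amend two entries in Table 3, keeping the present references to CT, MRI and post-mortem:

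- Ischaemic stroke: *without evidence of a new or enlarged intracerebral haemorrhage, compared with the index or latest earlier scan, that explains the deficit*.
- ICH: *with a corresponding new or enlarged intracerebral haemorrhage compared with the index or latest earlier scan*.

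State that the blinded adjudicators compare each event scan with the index imaging. Cases A and B then become ischaemic stroke, and case C no longer counts as ICH. Ischaemic stroke would still be defined by the absence of blood, so whether case C is a stroke at all remains a clinical judgement for the committee.

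The cost is a few words and one instruction to the committee. Index location and volume are already recorded and routine images already collected, so no new procedure is needed. As recruitment has begun, any event already adjudicated should be checked against the amended wording, still blinded to allocation.

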## Background

Stroke is a major cause of death and disability and is associated with high healthcare expenditure [1, 2]. About 80 % of strokes are ischaemic, 15 % intracerebral haemorrhage (ICH), and 5 % subarachnoid haemorrhage [3].

Cardioembolism, most often caused by non-valvular atrial fibrillation (AF), accounts for 13 to 27 % [4, 5] of ischaemic strokes. The average annual risk of ischaemic stroke in patients with AF not treated with antithrombotic drugs is 4.5 % [6]. The risk of ischaemic stroke can be estimated with the CHA_2_DS_2_-VASc score [7]. The annual thromboembolic event rate increases from 2.2 % with a CHA_2_DS_2_-VASc score of 2 to 15.2 % with the maximum score of 9 [8]. In patients with AF and a CHA_2_DS_2_-VASc score ≥ 1, treatment with an oral anticoagulant (OAC) is recommended [9, 10]. Traditionally, vitamin K antagonists (VKA) have been the first choice for prevention of thromboembolic events in these patients. While VKA therapy decreases the risk of ischaemic stroke, it increases the risk of ICH, the most devastating complication of OAC therapy. The risk of ICH in patients with AF treated with vitamin K antagonists is 0.3 to 3 % per year, and increases with increasing age [11–14]. This complication leads to death in 45 % of cases, and only 17 % of patients recover without disability [15].

In patients with AF who are unsuitable for VKA therapy because of poor compliance or allergy, or who are unwilling to receive this therapy, antiplatelet drugs (APDs, e.g. acetylsalicylic acid, clopidogrel) may be considered [9, 10]. However, antiplatelet treatment only results in a modest reduction in the risk of ischaemic stroke [16] and increases the risk of major bleeding as compared to no antithrombotic therapy (incidence rate ratio 1.55; 95 % confidence interval (CI), 1.48–1.63)) [17].

In patients with AF who survive an anticoagulation-related ICH, a longstanding and pressing clinical dilemma is whether or not to resume treatment with oral anticoagulation to prevent ischaemic stroke and other future thrombotic and embolic complications [18, 19]. Randomised trials have not been performed and reliable estimates of the risk of recurrent ICH or ischaemic stroke after resumption of antithrombotic drugs on the one hand, or permanent discontinuation of these drugs on the other, are lacking [20].

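### Table 3's 24-hour deficit rule has no alternative for earlier death, so an ICH or stroke fatal within a day falls outside the secondary ICH and stroke outcomes

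*Protocol article*

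**What the plan says.** All of this is in the protocol article, mostly under Study outcomes and in its Table 3.

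- ICH needs a new or worsened deficit "persisting for more than 24 hours, with a corresponding intracerebral haemorrhage on a CT or MRI scan or at post-mortem investigation".
- Ischaemic stroke needs a deficit "persisting for more than 24 hours, without evidence of a intracerebral haemorrhage on a CT or MRI scan or at post-mortem investigation".
- Unclassified stroke needs a deficit "persisting for more than 24 hours, without imaging or post-mortem investigations performed".
- Subarachnoid haemorrhage has no duration element: "Subarachnoid haemorrhage (SAH) demonstrated by CT, lumbar puncture, or at post-mortem investigation".
- Vascular death begins "Death from cerebral infarction; intracerebral, subarachnoid, epidural, or subdural haemorrhage" and goes on to unclassified stroke and other causes. It also covers sudden death within 1 hour of onset.

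The primary outcome is fixed thus: "The primary outcome is the combination of vascular death or non-fatal stroke (cerebral infarction, ICH, or subarachnoid haemorrhage) during follow-up". The secondary list includes "vascular death, death from any cause, all stroke, ischaemic stroke, ICH, other major extracranial haemorrhage", and its stroke and ICH items are not limited to non-fatal events. The Interim analyses section names ICH, together with fatal vascular events, as the main outcomes for harm.

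**The concern.** In the three affected definitions, duration and proof are separate requirements. Post-mortem examination can stand in for a scan, but it does not stand in for the 24 hours. A patient who dies 8 hours after onset has no deficit lasting longer than a day, however well the bleed is documented. Yet accepting autopsy proof only makes sense if fatal cases are meant to be included, so the rule works against its own evident purpose.

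What is at stake is the completeness of the secondary ICH and stroke rates. The Background makes comparison of recurrent ICH a secondary objective, and ICH is one of the two named harms. Any event lost this way is among the most severe.

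**Working it through.** **1. Definitions side by side.**

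| Table 3 entry | 24-hour rule | Early or fatal event provided for |
|---|---|---|
| Ischaemic stroke | yes | no |
| ICH | yes | no |
| Unclassified stroke | yes | no |
| Subarachnoid haemorrhage | no | not needed |
| Subdural, epidural haematoma | no | not needed |
| Myocardial infarction | no | yes, cardiac death before biomarkers |
| Major extracranial haemorrhage | no | yes, fatal bleeding qualifies |

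Only the three stroke entries with a duration rule leave the gap.

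**2. Follow one case: CT-proven ICH, death at 8 hours.**

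- ICH: not met, because 8 h < 24 h.
- All stroke: not met through ICH. It is not ischaemic (blood on the scan), not unclassified (imaging was done) and not subarachnoid.
- Intracranial haemorrhage: the Table 3 entry refers back to the ICH definition and so inherits the rule. The listed secondary outcome covers intracranial bleeds other than ICH.
- Major extracranial haemorrhage: does not apply.
- Vascular death and death from any cause: met. The case therefore enters the primary composite.

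Read literally, the case is in the primary outcome and in both death outcomes, but in no haemorrhage outcome.

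**3. The plan's own figure.** The sample size section gives 4.9 to 17.6 for 10 primary events in 100 patient-years. An exact binomial interval for 10/100 reproduces it (4.90 to 17.62); an exact Poisson interval would be 4.80 to 18.39. It concerns the primary outcome, and this point does not change it.

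**4. Size for the ICH outcome (illustration).** Let n be the true number of ICH per arm in 100 patient-years and f the share fatal within 24 hours. Expected loss = n × f. Both inputs are assumptions: n = 3, 5 or 8 and f = 5% to 30%. The values of n lie within the annual recurrent ICH ranges in the Background (2.5 to 20% after resuming vitamin K antagonists; 2.3 to 8.2% on acetylsalicylic acid or no antithrombotic), which the article itself calls unreliable. It gives no value for f.

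| n | f = 5% | 10% | 20% | 30% |
|---|---|---|---|---|
| 3 | 0.15 | 0.3 | 0.6 | 0.9 |
| 5 | 0.25 | 0.5 | 1.0 | 1.5 |
| 8 | 0.4 | 0.8 | 1.6 | 2.4 |

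The chance of losing at least one event is 1 − (1 − f)^n. For n = 5 this runs from 0.23 (f = 5%) to 0.83 (f = 30%).

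Exact Poisson limits for x events are χ²(0.025; 2x)/2 and χ²(0.975; 2x + 2)/2. For x = 5 they give 5 per 100 patient-years (1.6 to 11.7); for x = 4, 4 per 100 (1.1 to 10.2).

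**5. Comparison between arms.** With true rates a and b and the same f in each arm, the observed rates are (1 − f)a and (1 − f)b. Their ratio stays a/b; their difference shrinks to (1 − f)(a − b).

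**The case against.** The strongest reply is that the trial's main result is hardly touched. Vascular death includes death from ICH, cerebral infarction and unclassified stroke with no time condition, and the interim analyses use the same composite. The event at issue is also a fatal vascular event, the other named harm. Phase III planning is tied to the primary outcome rate, with ICH alone secondary. All of this stands.

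A reader might nevertheless infer that these deaths are lost from the primary outcome. That would require reading death from ICH through the Table 3 ICH definition, which would leave deaths between 1 and 24 hours without a clear place. The vascular death entry makes no such cross-reference, whereas the intracranial haemorrhage entry does. Ordinary cause-of-death attribution by the blinded committee is the natural reading.

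It can also be said that adjudicators will see the intent: the rule screens out deficits that resolve, and death is not resolution. That is plausible, so an actual loss is not demonstrated. But the article refers to Table 3 for the event definitions, and its Outcome adjudication section gives no rule for setting the duration element aside.

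A reader might also want the 24-hour rule dropped for scan-proven ICH whose deficit clears within a day. Requiring a persistent deficit is a legitimate choice of outcome, and nothing in the article contradicts it.

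**Conclusion.** The gap is real but limited. Three definitions, as written, exclude events fatal within 24 hours from the secondary ICH, ischaemic stroke and all-stroke outcomes. The absolute rates of those outcomes are understated by the share of such events. That share is unknown: under the assumed ranges above, the expected loss is 0.15 to 2.4 ICH per arm. Losing one of five leaves the estimate well inside its own confidence interval.

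Two stronger inferences fail. First, the Background says of ICH on vitamin K antagonists "This complication leads to death in" 45% of cases, but that figure has no time window and cannot supply a 24-hour share. Second, nothing shows that the treatment comparison is biased: with a similar early-fatal share in both arms, the hazard ratio is not systematically shifted. The conclusion assumes that Table 3 is applied literally and that vascular death is attributed by cause without the 24-hour condition.

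**What to change.** In the ischaemic stroke, ICH and unclassified stroke entries of Table 3, extend the duration requirement with the alternative *or leading to death*. Add one sentence stating that fatal events count in the ICH, ischaemic stroke and all-stroke outcomes. Leave the 24-hour rule for non-fatal events as it is.

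The cost is small: revised wording, notice to the adjudication committee, and possibly re-adjudication of a few early events. Sample size, treatment and the definition of the primary composite do not change.
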